### Health economics

The economic analysis will evaluate the feasibility of collecting resource use and health-related quality of life (HRQoL) data in people with long-term health conditions and sub-threshold depression. It will enable us to identify relevant resource use categories for the cost-effectiveness analysis and evaluate the feasibility and challenges of measuring costs and outcomes in the study population. The feasibility of collecting intervention costs and acquiring unit cost data for all resource use categories will be assessed. The primary analysis will focus on questionnaire completion rates and item-level rates of missing data at each time point for both resource use questionnaire and quality of life instruments. Also, the level of resource use and utility levels (and quality-adjusted life years) will be presented for each group. The feasibility of conducting a cost-effectiveness analysis using resource use and quality of life instruments data will be evaluated. A cost-utility analysis using the EQ-5D-3L and SF-12v2 responses which will be converted into utility scores using UK population algorithms [32] will be conducted. Then, the area under the curve approach will be used to calculate quality-adjusted life years (QALYs) for both groups. To estimate the incremental difference in costs and QALYs, a regression approach will be used which will control for baseline characteristics of patients, particularly baseline utility. The regression coefficient will provide the estimate of the incremental difference in QALYs and costs between the treatment and control arms. A bootstrap approach will be used to get the confidence interval around the incremental cost-effectiveness ratio. The results will be presented on the cost-effectiveness plane and as cost-effectiveness acceptability curve to evaluate the probability of being cost-effective against the commonly used willingness-to-pay threshold in the UK.

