**External pilot study:**

Objectives:Quantify the flow of participants (eligibility, recruitment and follow-up rate)Evaluate proposed recruitment, assessment and outcome measure collection methodsExamine the delivery of the enhanced support intervention in a community pharmacy setting (intervention uptake, retention and dose) to inform process evaluationProcess evaluation, using semi-structured interviews with participants across a range of socio-economic settings, and pharmacy staff to explore the acceptability of the ESI within community pharmacy, elements of the intervention that were considered useful (or not) and appropriateness of study procedures

Design: Pilot randomised controlled trial, including a prospective economic and qualitative evaluation

Setting: As above

Population: As above

Intervention: As above with adaptations post feasibility study

Comparator: Usual care

Sample size: 100 participants

Outcomes: Data will be used to estimate recruitment, intervention delivery and study completion rates as per objectives 2a–d. Definitive estimates of the effectiveness of ESI will not be made.

Primary outcome: Depression severity (Patient Health Questionnaire 9) at four months.

Secondary outcomes: Patient acceptance, uptake and attrition. ICD10 depression status, anxiety (GAD 7), health-related quality of life (SF-12v2) and health-state utility (EQ5D 3L) will be measured at four months.

Economic evaluation: The incremental cost per QALY will be calculated from both the NHS and societal perspective.

Process evaluation: Using mixed methods, potential mediators/moderators of the intervention, the acceptability (to participants and pharmacy staff), barriers and facilitators to the use of ESI in community pharmacy, and impact on usual practice will be examined. Semi-structured interviews with approximately 30 study participants, 20 pharmacy staff and eight GPs near participating pharmacies will be conducted.

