### Randomisation and allocation concealment

Individual independent randomisation will be used. Randomisation will be carried out by the York Trials Unit (YTU), University of York, online randomisation service (URL:www.yorkrand.com/), independently of the trial team. One hundred participants will be randomised on a 1:1 basis to either the intervention group (50) or control group (50) following completion of the baseline interview.

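### The planned bootstrap confidence interval for the ICER is likely to have no clear meaning in a pilot of this size; intervals for incremental cost, QALYs and net benefit should replace it (minor)

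*Protocol article*

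**What the plan says.** In the Health economics section, QALYs are derived so that "the area under the curve approach will be used to calculate quality-adjusted life years (QALYs) for both groups". For the incremental differences in cost and QALYs, "a regression approach will be used which will control for baseline characteristics of patients, particularly baseline utility". The next step is fixed without condition: "A bootstrap approach will be used to get the confidence interval around the incremental cost-effectiveness ratio". The section then adds: "The results will be presented on the cost-effectiveness plane and as cost-effectiveness acceptability curve to evaluate the probability of being cost-effective".

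The same section sets the priority of these outputs: "The primary analysis will focus on questionnaire completion rates and item-level rates of missing data at each time point". The abstract announces the ratio itself: "The incremental cost per QALY will be calculated from both the NHS and societal perspective". For the pilot as a whole it also says: "Definitive estimates of the effectiveness of ESI will not be made".

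The Sample size section assumes 20% loss from 100 randomised, which leaves 80 measured. Randomisation is 1:1, so about 40 per arm are measured. The warning that a result is unreliable appears under Outcome and data storage and analysis and covers the primary-outcome (PHQ-9) test. The Health economics section does not repeat it.

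**The concern.** An ICER is a ratio whose denominator, the QALY difference, may be positive, negative or near zero. It is not ordered across the cost-effectiveness plane. A negative value can mean cheaper and better or dearer and worse. A positive value can mean dearer and better or cheaper and worse, which call for opposite decisions at a given threshold. When replicates lie on both sides of zero QALY difference, percentiles of the ratios no longer run from favourable to unfavourable, and the limits cannot be read as a range of plausible cost per QALY.

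At stake is the reporting of one statistic. The article does not say what will be reported if replicates span zero. It names two utility sources (EQ-5D-3L and SF-12v2) and two cost perspectives, so up to four such intervals could appear, none with the warning given to the PHQ-9 comparison.

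**Working it through.** **The plan's own figure.** For 20% attrition in 100 participants, the half-width is 1.96 × √(0.20 × 0.80 / 100) = 0.078, or about 8 points, giving 12 to 28% as stated. Measured participants: 100 × 0.80 = 80, or 40 per arm. Both reproduce. The article gives no figure for the QALY difference, its SD or the ICER.

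**Inputs from the article.** 40 measured per arm; utility at baseline and 4 months (T = 1/3 year); area-under-the-curve QALYs; adjustment for baseline utility.

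**Assumed inputs.** Utility SD 0.20 to 0.30; correlation r between baseline and 4-month utility 0.5 to 0.7; true utility gain 0.02 to 0.05.

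**Formulas.** With two time points and baseline adjustment:

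- QALY difference = (T/2) × utility gain = gain / 6.
- SE = SD × √(1 − r²) × √(2/40) / 6.
- With z = QALY difference / SE, the expected share of replicates with a negative QALY difference is Φ(−z).
- P(95% interval includes zero) = Φ(1.96 − z) − Φ(−1.96 − z).

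**Results.**

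| SD | r | SE (QALY) | Utility gain | QALY gain | Negative replicates | P(interval includes 0) |
|---|---|---|---|---|---|---|
| 0.20 | 0.7 | 0.0053 | 0.05 | 0.0083 | 6% | 65% |
| 0.20 | 0.7 | 0.0053 | 0.02 | 0.0033 | 27% | 90% |
| 0.30 | 0.5 | 0.0097 | 0.05 | 0.0083 | 19% | 86% |
| 0.30 | 0.5 | 0.0097 | 0.02 | 0.0033 | 37% | 94% |

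First row: SE = 0.20 × √0.51 × 0.2236 / 6 = 0.0053; z = 0.0083 / 0.0053 = 1.57; Φ(1.96 − 1.57) = 0.65.

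**Wider assumptions, stated as residual SD after baseline adjustment.** P(interval includes 0), 40 per arm:

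| Utility gain | SD 0.10 | SD 0.15 | SD 0.20 | SD 0.25 |
|---|---|---|---|---|
| 0 | 95% | 95% | 95% | 95% |
| 0.02 | 86% | 91% | 93% | 94% |
| 0.05 | 39% | 68% | 80% | 86% |
| 0.10 | 1% | 15% | 39% | 57% |

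An 80% chance of excluding zero needs a true utility gain of 0.063, 0.094, 0.125 or 0.157 respectively.

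**What the ratio interval looks like.** One percentile-bootstrap illustration used 40 per arm, 5,000 replicates, an assumed cost difference of 100 and an assumed cost SD of 800. With a utility gain of 0.05 and residual SD 0.20, the replicates split as follows: 57% dearer and better, 27% cheaper and better, 13% dearer and worse, 3% cheaper and worse. The ICER was 12,000 (100 / 0.0083) with a percentile interval of about −206,000 to +207,000. Its negative part mixes dominant with dominated replicates. From the same replicates, the probability of positive net benefit at an assumed 20,000 per QALY was well defined, at 0.60.

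**The case against.** Four points can be made for the plan.

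- **The effect is unknown.** The article gives no utility effect, SD or correlation. A reader might infer that the QALY difference is bound to straddle zero and the interval bound to be uninterpretable. The article does not support that: with a gain of 0.10 and residual SD 0.10, the chance is 1%. This stands, so the claim is one of likelihood.
- **The construction is not specified.** The article says only that a bootstrap will be used, and the interval type may be set out in a fuller document. This stands in part: the percentile interval above is an illustration. But no construction gives a clean bounded ratio interval when the denominator plainly includes zero, and the commitment to an interval for the ratio is already made.
- **Valid displays are already planned.** The plane and acceptability curve come from bootstrap replicates and can be read across all four quadrants. At a given threshold, the curve is the probability that net benefit is positive. This stands and limits the harm. It does not make the ratio interval valid.
- **The output is secondary.** The section is framed as feasibility work, its primary analysis is completeness of data, and the abstract disclaims definitive estimates of effectiveness. A reader might infer that the interval could mislead a stop/go decision. No progression rule in the article uses cost-effectiveness; the Dissemination section says only that results will inform whether and how a full trial is practical.

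**Conclusion.** The point holds as a minor one. The article commits to an interval for the ICER in a design where the 95% interval for the QALY difference is likely to include zero: about 65 to 94% of trials under a utility SD of 0.20 to 0.30, correlation of 0.5 to 0.7 and gain of 0.02 to 0.05. Those three ranges are assumptions, and larger gains or smaller residual SDs bring the figure down. The protocol's own expectation that effectiveness is unlikely to be established on the PHQ-9 offers no reason to expect a clearer result on QALYs. The fault lies in the ratio interval alone. It does not reach the regression estimates of incremental cost and QALYs, the plane or the acceptability curve.

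**What to change.** Drop the confidence interval for the ICER. Report incremental cost, incremental QALYs and incremental net monetary benefit (threshold × QALY difference − cost difference) at the UK threshold the section already refers to, each with a bootstrap 95% interval. Resample each participant's cost and QALY together within arm, and refit the baseline-adjusted regressions in every replicate. Keep the plane and the acceptability curve. Extend to the cost-utility results the warning now attached to the PHQ-9 test.

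The cost is a change of wording in the analysis plan. No new data are needed, and net benefit comes from the same replicates.

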### Process evaluation

As per UK MRC recommendations, a mixed methods approach to process evaluation [33] will be used to consider fidelity, implementation, mechanisms and context. Descriptive statistics will be used to describe elements of the intervention (participants, dose and intervention content). The moderational analysis will examine baseline variables that may moderate outcomes such as age, depression onset age, number of episodes and socioeconomic status. The mediational analysis will investigate hypothesised mechanisms of change such as number of sessions, content of scheduled contacts (from pharmacy ESI facilitator records) and changes in activation (BADS) using established methodology [34]. As this is an external pilot RCT, it is considerably underpowered to undertake these evaluations so data will be summarised and used to refine process evaluation design to inform a future large-scale definitive RCT.

A process evaluation using qualitative methods will be used to explore acceptability and important elements of the intervention from the perspective of the participants. A purposive sample of approximately 15 participants who completed the intervention will be invited to participate in a semi-structured interview (recruitment and data collection will continue until category saturation has been achieved). Sampling will ensure that participants with a range of age and gender are sampled and from a range of socio-economic groups. The interviews will explore the acceptability of case-finding for sub-threshold depression, receiving the enhanced support intervention (ESI) within a community pharmacy setting, impact on relationship with general practice and research procedures. A sample of participants who dropped out (had less than two sessions) will also be invited to participate in a semi-structured interview to explore reasons for drop out. It is likely approximately 15 interviews will be needed to achieve data saturation [35].

Sampling will be ensured in areas of higher deprivation (i.e. bottom two quintiles of index of multiple deprivation (IMD)), to enable us to explore perspectives of people particularly from lower socioeconomic status (SES). Perceptions of the appropriateness of the intervention for people with poor health literacy and from lower socioeconomic status (SES) will be explored. All interviewees will be interviewed at a time and place convenient to them (e.g. at home, in the pharmacy, GP surgery or by telephone).

Interviews with patient participants will be conducted after the primary outcome data has been collected.

Interviews with approximately 20 pharmacy staff (across a broad range of pharmacy roles) will examine acceptability and important elements of the intervention, training and supervision, barriers/facilitators to participation and implementation, and impact on pharmacy practice.

Interviews with approximately eight local GPs will explore knowledge and perspectives of the intervention, impact on routine practice and how this intervention might be implemented in practice.

Semi-structured interviews offer opportunities to cover in-depth, a range of topics relevant to the research questions, whilst also allowing for exploration and probing of additional issues raised during the interviews. Interviews topic guides will vary by group; these may be amended iteratively as interviews progress but will contain core questions highlighted in the feasibility study. Interviews will last up to an hour and will be digitally recorded with consent and transcribed verbatim, the transcripts forming the data for analysis. Coding will be undertaken independently by members of the qualitative research team with meetings to ensure emerging codes remain grounded in the original data. Initial analysis will use the principles of constant comparison, which will allow modification of the topic guides and analysis across the data sets [34]. Further analysis will use the principles of framework analysis and NPT [26].

### Process evaluation—recruitment

Recruitment of patient participants will be as described in the feasibility study above.

ESI facilitators will be provided with the staff participant information sheet and consent form upon completion of their intervention training. Remaining pharmacy staff will be contacted by letter and provided with the same study information. A reminder letter will be sent once the intervention delivery has commenced in each participating pharmacy. All pharmacy staff will be provided with pre-paid envelopes to return the consent form directly to the study team. Processes will ensure participation is confidential and free from any coercion by employers or co-workers.

The GPs of recruited participants and GPs in participant identification sites will be contacted by letter and invited to take part. They will be provided with a participant information sheet, consent form and pre-paid envelope to return to the study team.

### CHEMIST study governance

The study will be led by the Chief Investigator (DE) with day-to-day management provided by the Trial Manager (EL). There will be an independent Trial Steering Group (TSG) and Data Monitoring and Ethics Committee (DMEC) as per NIHR recommended constitution. The sponsor will provide oversight and audit of the study as per local standard operating procedures. Serious adverse events will be collected and monitored as per local standard operating procedures.

Protocol amendments will be managed via the Health Research Authority, Research Ethics Committee and sponsor approvals process during the study.

### Dissemination

The study will be disseminated via peer-reviewed journals and conference presentations. Plain English summaries will be produced and distributed via partner stakeholders and to study participants. Results will be used to assess if and how a fully powered RCT is practical.

## Discussion

Community pharmacies are increasingly used to deliver health promotion activities and have regular contact with people with long-term health conditions. The use of community pharmacy in research, and in particular in depression research, is new and as such requires testing prior to conducting large scale randomised controlled trial. The CHEMIST feasibility and pilot RCT study is an innovative design in this novel area. The methods outlined will produce data on how and if future trials might be conducted and will be disseminated through conference presentation and peer-reviewed open access publication.

### CHEMIST study status

At time of writing the CHEMIST study is still in its recruitment phase and process evaluation has commenced.

## Abbreviations

BA: Behavioural activation
CI: Confidence interval
CP: Community pharmacy
DMEC: Data Monitoring and Ethics Committee
DNA: Did not attend
DOB: Date of birth
ESI: Enhanced support intervention
GP: General practice
GPs: General practitioner
ICC: Intraclass correlation coefficient
IMD: Index of multiple deprivation
LTC: Long-term conditions
MINI: Mini International Neuropsychiatric Interview
NHS: National Health Service
NIHR: National Institute of Health Research
NPT: Normalisation Process Theory
PHR: Public Health Research
QALY: Quality-adjusted life year
RCT: Randomised controlled trial
SD: Standard deviation
SES: Socioeconomic status
SOP: Standard operating procedure
TSG: Trial Steering Group
YTU: York Trials Unit
